### Secondary Outcomes

All secondary outcome measurements will be obtained just before inclusion (in the usual care screenings program) and one year after inclusion. The secondary outcome measurements include clinical responses to drug therapy (eg, cholesterol level), self-report questionnaires, and changes in systolic blood pressure.

Clinical responses to drug therapy will be recorded. A recorded low-density lipoprotein cholesterol level above 20% of preestimated low-density lipoprotein cholesterol reduction during follow-up will be considered as possible indication of poor adherence. If the patient also uses antihypertension drugs, the blood pressure on baseline will be compared to blood pressure after one year and will need to be within target blood pressure for cardiovascular risk management (systolic <135 mm Hg). These office blood pressure measurements are performed according to the recommendations of the European Society of Hypertension [15] with a validated automated device; data will be based on a mean of four office measurements.

Second, two validated self-report questionnaires will be used. The MMS will be used to measure adherence [17]. Each of the 8 items measures a specific medication‐taking behavior. MMS scores can range from 0 to 8 and can be classified into three levels of adherence: low adherence (score of less than 6), medium adherence (score of 6 to less than 8) and high adherence (score of 8) [31]. The BMQ will be used to provide information about the beliefs, perceived necessity, and concerns patients have regarding their illness and prescribed medication [18]. Respondents indicate their degree of agreement with each individual statement about medicines on a 5‐point Likert scale. It is then possible to differentiate between patients on the basis of their beliefs about the necessity of their medication and their concerns about taking it. Patients can be classified into four different categories: accepting (high necessity and low concerns), ambivalent (high necessity and high concerns), skeptical (high concerns and low necessity), and indifferent (low concerns and low necessity) [32,33].

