## Methods

### Study Setting

Participants will be drawn from a hospital‐wide screening program. This screening program is situated at the cardiovascular outpatient clinics in an academic medical center in Nijmegen, the Netherlands. All new patients diagnosed in the last 6 months with acute coronary syndrome, peripheral arterial disease, an aneurysm of the aorta, or stroke/transient ischemic attack (TIA) and referred to the departments of vascular surgery, neurology, or cardiology are automatically included in this program.

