#### Usual Care (Groups I, II, and III)

All new CVD patients receive the hospital‐wide screening program according to the Dutch guidelines [14] (based on the European guidelines [15]). The screening assesses cardiovascular risk factors in all patients with CVD. It screens for lifestyle risk factors, blood lipid levels, blood pressure, waist circumference, body mass index, blood glucose levels, and a family history of CVDs. Lifestyle is evaluated through a questionnaire which is a compilation of existing validated questionnaires regarding demographic data, smoking, alcohol use, physical activity, and eating habits. For each of these lifestyle issues, the patient’s motivation to change is evaluated [16]. Adherence is measured by the Modified Morisky Scale (MMS) [17] and the Beliefs about Medication Questionnaire (BMQ) [18]. Medication use will be monitored. If necessary and if the patients agree they attend consultations with a nurse based on motivational interviewing to help them lose weight, stop using alcohol, or stop smoking.

According to European guidelines [15], all patients with established CVDs (this means all participants of this trial) should have antiplatelet therapy (eg, aspirin or clopidrogel) and a lipid lowering drug (eg, simvastatin or atorvastatin). The use of antihypertensive drugs is dependent on the systolic blood pressure. Except for the specific additions for the study, all participating and nonparticipating patients receive the same regular preventive cardiovascular care including monitoring of medication use. All patients receive regular vascular care from their medical specialist.

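### The LDL flag for poor adherence compares a level with a fraction of a change, so followed literally it marks essentially every patient, full adherers included

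*Protocol article*

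**What the plan says.** The rule is one sentence in the Secondary Outcomes section of the protocol article: "A recorded low-density lipoprotein cholesterol level above 20% of preestimated low-density lipoprotein cholesterol reduction during follow-up will be considered as possible indication of poor adherence". The comparison at issue lies in the words "lipoprotein cholesterol level above 20% of preestimated". The article does not say how the reduction is predicted or from which LDL value.

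Three other statements bear on it.

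- The same section lists the outcomes themselves: "The secondary outcome measurements include clinical responses to drug therapy (eg, cholesterol level), self-report questionnaires, and changes in systolic blood pressure". The cholesterol level is thus named as a clinical response in its own right.
- On timing, "All secondary outcome measurements will be obtained just before inclusion", in the usual-care screening, and again one year later. Statistical Methods compares the change from first to last time-point between groups for primary and secondary outcomes, and presents laboratory results quantitatively.
- On treatment background, the Usual Care section says that under the European guidelines "all patients with established CVDs (this means all participants of this trial) should have antiplatelet therapy", and the sentence goes on to include a lipid-lowering drug. Study Setting describes the source population as "All new patients diagnosed in the last 6 months" with one of the listed cardiovascular conditions.

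**The concern.** The left side of the rule is a level. The right side, "above 20% of preestimated low-density lipoprotein cholesterol reduction", is a fraction of a change. If the reduction is in mmol/L, the threshold is a very small number that almost no LDL value falls below. If it is a percentage, the two sides do not share a unit. A flag that is positive in nearly everyone has almost no specificity and gives no contrast between arms.

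The likely intentions are easy to guess, but there are two of them and they do not agree in general. If the choice is left until results are in, it is made with the flag rates in view.

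A second difficulty is the reference value. A predicted reduction must be predicted from some LDL. The only baseline that the article fixes is the screening value, and some patients may already be on a lipid-lowering drug by then.

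**Working it through.** The plan states no figure for this rule, so there is nothing to reproduce. All LDL values and reductions below are assumptions.

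**1. The literal rule.** Let B be the reference LDL and f the predicted fractional reduction.

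- Threshold: 0.2 × f × B.
- Level of a full adherer who meets the prediction: (1 − f) × B.
- Ratio of level to threshold: (1 − f) / (0.2 f). B cancels.
- That patient is flagged when 1 − f > 0.2 f, that is f < 1/1.2 = 83.3%.

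| f | (1 − f) / (0.2 f) | Ratio |
|---|---|---|
| 30% | 0.70 / 0.06 | 11.7 |
| 40% | 0.60 / 0.08 | 7.5 |
| 50% | 0.50 / 0.10 | 5.0 |
| 80% | 0.20 / 0.16 | 1.25 |

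Example with B = 3.5 mmol/L and f = 40%: the threshold is 0.2 × 0.4 × 3.5 = 0.28 mmol/L, and the full adherer's level is 0.6 × 3.5 = 2.10 mmol/L.

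**2. Allowing for variation between patients.** A simulation of 400,000 patients per cell used B from a normal distribution with mean 3.5 and SD 0.9 mmol/L, and an individual reduction at full adherence with mean f and SD 0.12, multiplied by adherence. Adherence had nominal means of 65%, 75% and 85% in groups I, II and III with SD 30% (from Sample Size), with values outside 0 to 1 set to the limit. Under the literal rule the flag rate is 100.0% to one decimal in every arm and among full adherers for f of 30%, 40% and 50%. At f = 60% it is 99.9%, 99.8% and 99.7% in groups I, II and III, and 99.0% among full adherers.

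**3. The two coherent readings.**

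- Reading A, level more than 20% above the predicted level: flagged when the achieved fractional reduction is below 1 − 1.2(1 − f) = 1.2f − 0.2.
- Reading B, achieved reduction more than 20% short of the predicted one: flagged when it is below 0.8f.

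The cut-offs agree only when 1.2f − 0.2 = 0.8f, that is f = 50%. At f = 30% they are 0.16 and 0.24; at f = 40%, 0.28 and 0.32. Flag rates in the same simulation:

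| f | Reading | I | II | III | Full adherers |
|---|---|---|---|---|---|
| 30% | A | 44.2% | 35.2% | 27.9% | 12.2% |
| 30% | B | 69.3% | 61.0% | 53.3% | 30.8% |
| 40% | A | 60.3% | 50.2% | 41.0% | 15.8% |
| 40% | B | 70.2% | 61.1% | 52.3% | 25.1% |
| 50% | A or B | 70.4% | 60.9% | 51.4% | 20.3% |

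Both readings separate the arms under these assumptions. The literal rule does not.

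**4. The reference value.** Take a full adherer with untreated LDL 3.5 mmol/L and f = 40% who is already treated at screening and does not change. Screening and one-year LDL are both 2.10 mmol/L. If the prediction is applied to the screening value:

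- Reading A: the limit is 1.2 × 0.6 × 2.10 = 1.51 mmol/L, and 2.10 exceeds it.
- Reading B: the required fall is 0.8 × 0.4 × 2.10 = 0.67 mmol/L, and the achieved fall is 0.

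This full adherer is flagged either way.

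**The case against.** The strongest reply is that little hangs on the sentence. The flag is worded only as something that "will be considered as possible indication of poor adherence", and Statistical Methods never names it as a variable to be tested. Low adherence in the logistic regression is defined by refill data, and the ROC analysis sets the questionnaires against refill data. This stands, and it limits the finding.

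A reader might go further and infer that the clinical-response outcome as a whole cannot separate the arms. The article does not support that. The cholesterol level is itself listed as a clinical response, its change is compared between groups, and systolic blood pressure is assessed separately. Nor does the article make LDL the only biochemical secondary outcome: cholesterol is given as an example, and blood glucose is also recorded at screening.

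A second reply is that the ambiguity matters little for the arm contrast. At f = 40% the difference between groups I and III is 60.3 − 41.0 = 19.3 points under Reading A and 70.2 − 52.3 = 17.9 under Reading B. That is fair for these inputs. The shares flagged still differ, by 10 points in group I at f = 40% and by 25 at f = 30%, and the flag is meant to classify individuals.

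A third reply is that the method of prediction may be in the full protocol. It may, so its absence here is not the point. The comparison that is stated is wrong as it stands. It would also be too strong to say that all patients are treated at screening: the Usual Care section says what patients should have under guidelines, and gives no treatment status at that visit.

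**Conclusion.** The point holds for the dichotomous LDL flag. As written, the flag is effectively constant: any patient who exactly meets a predicted reduction below 83.3% is flagged, whatever the reference LDL. That step is algebra and needs no LDL data. The factor of 5 to 12 rests on assumed reductions of 30% to 50%, and the simulated rates rest on the distributions stated with them. Because extreme individual responses can fall below the threshold, the accurate wording is essentially every patient, not every patient without exception.

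The reference-value problem is real for patients already treated at screening, but the article does not give their share, so its size is unknown. The continuous LDL comparison, the blood pressure outcome, the primary refill outcome and the sample size are untouched. This is a clear error in a secondary measure that is cheap to correct.

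**What to change.** Do one of two things before any outcome data are seen.

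- Drop the flag.
- Restate it on a single scale, either as a level against a predicted level or as an achieved reduction against a predicted reduction. Name the reference LDL and how the reduction is predicted from it, limit the flag to patients who have that reference value, and label it descriptive.

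In either case, state that the lipid secondary outcome is the one-year LDL as a continuous variable, compared between the three arms with adjustment for the screening LDL. A between-arm comparison of change is already planned; this makes explicit which variable carries the lipid result.

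The cost is a rewritten sentence. The continuous analysis needs no new data, because LDL is already due at screening and at one year. The small downside is that a retained flag would be available only for patients with the reference value on record.

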#### Website (Groups II and III)

The website contains an individualized Web portal called Interactive File Vascular Care (Interactive Dossier Vaatzorg, or iVAZ). This is developed to support patient-based self-evaluation and management [19,20]. Patients can log on and see their own cholesterol levels, blood pressure, and lifestyle (smoking habit, exercise, and eating habits) in a risk monitor. Patients can ask questions by email to their nurses, and they can enter changes in their medication. iVAZ provides risk communication, the feedback of clinical outcome will be provided individually, and patients are invited to be active in managing their illness and medication.

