### Data Collection and Management

The primary data collected will be provided by the initial screening. Obtained data from the screening are blood lipid levels, blood pressure, waist circumference, body mass index, blood glucose levels, and medication use. Lifestyle is evaluated through a questionnaire which is a compilation of existing validated questionnaires regarding demographic data, smoking, alcohol use, physical activity, and eating habits. For each of these lifestyle issues, patient’s motivation to change is evaluated [16]. Adherence is measured by the MMS [17] and beliefs about medication by the BMQ [18].

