### Statistical Methods

The data will be analyzed based on the intention‐to‐treat principle and evaluated using SPSS, with descriptive statistics (mean, median, SD, and interquartile range) being determined for all variables. The data will be presented in quantitative format (eg, biometrics, laboratory results, blood pressure, lifestyle scores, adherence score on the basis of refill data, and the MMS) and in descriptions of observed effects (eg, change in BMQ, determinants for adherence, evaluation of the use of iVAZ, and appreciation of nurse intervention).

To evaluate the difference between the groups, an analysis of variance test will be performed on the outcome measures for the three patient groups. The independent variable will be the three intervention groups. The dependent variable is medication adherence measured with the dedicated calculation of refill data. Specifically, we will compare the difference between the first and last time-point between groups for the primary and secondary outcomes measures. For the intervention groups II and III, we will also compare the outcomes of the clinical data at 16 and 28 weeks. To correct for multiple comparison, a Duncan’s multiple range test will be performed. Furthermore, we will perform a receiver operating characteristic (ROC) curve analysis to compare the outcome of the screening instruments (MMS and BMQ) with the pharmacy refill dates. In the ROC curve plot, specificity of the questionnaire is on the x-axis and sensitivity of the question is on the y-axis.

Plausible relations between parameters of cardiovascular risk factors, motivation to change, socioeconomic class, and parameters of adherence (calculated refill score and BMQ and MMS scores) will be tested in a univariate manner. Individual parameters will be tested for normality using the Kolomogorov-Smirnov test in order to select adequate univariate tests. Multiple logistic regression analysis will be performed to assess the relative importance of selected parameters for the likelihood of low adherence, as defined by the refill data algorithm. In all analyses, potential confounders will be included if they independently changed the beta coefficient for dedicated calculation of refill data by at least 5% or when consensus about inclusion existed within the team of researchers supported by clinical evidence from literature.

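### The blood-pressure secondary outcome is stated in two ways, and the plan does not say when antihypertensive use is judged

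*Protocol article*

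**What the plan says.** All statements are in the protocol article.

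- **Secondary Outcomes, opening paragraph.** The outcomes include "self-report questionnaires, and changes in systolic blood pressure", with no limit to drug users. On timing: "All secondary outcome measurements will be obtained just before inclusion (in the usual care screenings program) and one year after inclusion".
- **Secondary Outcomes, next paragraph.** The comparison becomes conditional: "If the patient also uses antihypertension drugs, the blood pressure on baseline will be compared to blood pressure after one year". The same sentence adds that the pressure "will need to be within target blood pressure for cardiovascular risk management (systolic <135 mm Hg").
- **Usual Care.** "The use of antihypertensive drugs is dependent on the systolic blood pressure".
- **Website.** Patients in groups II and III have a portal where "they can enter changes in their medication".
- **Data Collection and Management.** The initial screening records "blood lipid levels, blood pressure, waist circumference, body mass index, blood glucose levels, and medication use".
- **Statistical Methods.** "The data will be analyzed based on the intention‐to‐treat principle". Primary and secondary outcomes are compared between groups as the difference from first to last time-point. The section does not separately define who is in the blood-pressure analysis.

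**The concern.** Within one section, two things change between consecutive paragraphs: who is in the outcome (everyone, or users of antihypertensives) and what the endpoint is (change in systolic pressure, or being below a threshold at one year). A reader cannot tell which comparison the trial will report.

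The condition also has no date. It is in the present tense and governs a comparison that runs from screening to one year. This matters more here than in most trials. Usual care ties antihypertensive use to systolic pressure, so use during follow-up could follow from the outcome itself. The intervention is meant to change drug taking, so continued use could also follow from the arm. If users were identified at follow-up, the analysis set would be selected on a state that arises after randomisation. Patients who stopped would be removed, more of them from the arm with worse adherence, and patients started because their pressure rose would be added. A measure presented as a clinical response to therapy would then miss the patients in whom non-adherence shows.

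**Working it through.** The plan gives no sample size, SD, stopping rate or number of users for blood pressure, so there is no figure of its own to reproduce. The check has three parts.

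**1. The two statements side by side**

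| | Opening paragraph | Next paragraph |
|---|---|---|
| Population | not restricted | patients using antihypertensives, no date |
| Endpoint | change in systolic pressure | baseline against one year, and below 135 mm Hg |

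The condition can be read in three ways:

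- **Use at screening.** The data exist, nobody leaves the set later, and the result is a legitimate subgroup.
- **Use at one year.** Stoppers leave and starters enter.
- **Use at any time.** Stoppers stay and starters enter.

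The second and third depend on what happens after randomisation. No sentence chooses among the three.

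**2. What the one-year reading would do (all inputs assumed)**

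Let s_C and s_I be the proportions of screening users who stop in control and intervention, e the systolic rise on stopping, and m and SD the one-year mean and SD on drug. The arms differ only in stopping, and stopping is independent of pressure.

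- All screening users, difference in means: (s_C − s_I) × e.
- All screening users, difference on target: (s_C − s_I) × [Φ((135 − m)/SD) − Φ((135 − m − e)/SD)].
- Users still on drug at one year: mean m in both arms, so both differences are 0.

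*First set of assumptions.* Screening pressure has mean 140 and SD 18. One-year pressure is 137 + 0.6 × (screening − 140) plus residual SD 14. Then m = 137 and SD = √(0.6² × 18² + 14²) = √312.64 = 17.7.

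- 20% v 10% stopping, e = 10: 0.10 × 10 = 1.0 mm Hg; 0.10 × (0.455 − 0.249) = 2.1 points.
- 30% v 15%, e = 8: 0.15 × 8 = 1.2 mm Hg; 0.15 × (0.455 − 0.286) = 2.5 points.
- 30% v 15%, e = 12: 0.15 × 12 = 1.8 mm Hg; 0.15 × (0.455 − 0.214) = 3.6 points.

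*Second set, for range.* m = 130, SD 15, control stopping 10% to 30% with half that in the intervention arm, e from 5 to 15 mm Hg. The differences among all screening users run from 0.05 × 5 = 0.25 to 0.15 × 15 = 2.25 mm Hg, and from 0.7 to 5.7 points.

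In every row the difference among current users is 0. Starters are not modelled, so their effect is not quantified.

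**3. Size against noise**

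Under the first set, the SD of change is √(0.4² × 18² + 14²) = √247.84 = 15.7 mm Hg. With 200 per arm all using antihypertensives, the standard error of a difference is 15.7 × √(2/200) = 1.57 mm Hg. A loss of 1.0 to 1.8 mm Hg is therefore 0.6 to 1.1 standard errors, and less with fewer users. Adjusting for screening pressure leaves SD 14 and a standard error of 14 × √(2/200) = 1.40 mm Hg (the small spread added by stopping is ignored in both).

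**The case against.** The strongest reply is that the condition most naturally means patients prescribed an antihypertensive alongside the antiplatelet and lipid-lowering drugs that all participants should have. Usual Care describes an indication for treatment and says nothing about follow-up or arm. Medication use is recorded at screening, so that reading is workable and loses no stoppers. A check on drug response that dropped those who stopped would also defeat itself, which makes the one-year reading less likely to be intended. All of this stands.

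A second reply is that the conditional sentence may only elaborate the item on clinical response to therapy, leaving unrestricted systolic change as a separate outcome under the intention-to-treat rule. That is possible. But the text does not say there are two blood-pressure outcomes, and a reader is left to guess which one is reported.

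A third is that an analysis set for one secondary outcome is commonly left to the analysis plan. That would answer silence. Here the article makes two statements that do not match.

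Finally, the illustration is built on assumed inputs, and the zero among current users follows from the set-up. That also stands. It shows what selecting on later use would do, not that the plan does so.

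**Conclusion.** The point holds as an inconsistency and an undated condition. On any reading, the section does not settle who is in the blood-pressure outcome or which endpoint applies.

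A reader might infer that the plan removes patients who stop their drugs from the outcome meant to detect them. The documents do not support that. No sentence places the judgement of use at one year, and read as use at screening the condition removes nobody. What can be said is that the wording permits selection after randomisation. If it were applied that way, the comparison would conflict with the stated intention-to-treat principle.

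The size is illustrative: about 1 to 2 mm Hg and 2 to 4 percentage points on target under the first set of assumptions, with a wider range of 0.25 to 2.25 mm Hg and 0.7 to 5.7 points under the second. These are modest beside the sampling error that the trial would have for this outcome. The plan should be corrected here, but the issue concerns a secondary outcome only. The refill-based primary outcome and the sample size do not depend on it.

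**What to change.** Replace the two statements with one analysis, for example:

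*Systolic pressure at one year will be analysed as a continuous outcome, adjusted for systolic pressure at screening, in all randomised patients and in the subgroup with an antihypertensive recorded at screening. Patients are analysed in their randomised arm whether or not drugs are later stopped or started. The proportion on target at one year will be reported descriptively.*

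The all-patient analysis matches the opening list and the intention-to-treat rule. The subgroup keeps the question that the conditional sentence asks, in a set fixed before randomisation. Adjusting for screening pressure replaces the raw change and is somewhat more precise under the assumptions above (standard error 1.40 against 1.57 mm Hg).

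The cost is a short rewording of the outcome and its analysis. Screening medication and pressure are already collected, and the one-year pressure is already planned. One small downside is that patients who start a drug after randomisation count only in the all-patient analysis.
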